## Abstract

**Background:**

Elderly patients discharged from hospital experience fragmented care, repeated and lengthy emergency department (ED) visits, relapse into their earlier condition, and rapid cognitive and functional decline. The Acute Care for Elders (ACE) program at Mount Sinai Hospital in Toronto, Canada uses innovative strategies, such as transition coaches, to improve the care transition experiences of frail elderly patients. The ACE program reduced the lengths of hospital stay and readmission for elderly patients, increased patient satisfaction, and saved the health care system over Can $4.2 million (US $2.6 million) in 2014. In 2016, a context-adapted ACE program was implemented at one hospital in the Centre intégré de santé et de services sociaux de Chaudière-Appalaches (CISSS-CA) with a focus on improving transitions between hospitals and the community. The quality improvement project used an intervention strategy based on iterative user-centered design prototyping and a “Wiki-suite” (free web-based database containing evidence-based knowledge tools) to engage multiple stakeholders.

**Objective:**

The objectives of this study are to (1) implement a context-adapted CISSS-CA ACE program in four hospitals in the CISSS-CA and measure its impact on patient-, caregiver-, clinical-, and hospital-level outcomes; (2) identify underlying mechanisms by which our context-adapted CISSS-CA ACE program improves care transitions for the elderly; and (3) identify underlying mechanisms by which the Wiki-suite contributes to context-adaptation and local uptake of knowledge tools.

**Methods:**

Objective 1 will involve staggered implementation of the context-adapted CISSS-CA ACE program across the four CISSS-CA sites and interrupted time series to measure the impact on hospital-, patient-, and caregiver-level outcomes. Objectives 2 and 3 will involve a parallel mixed-methods process evaluation study to understand the mechanisms by which our context-adapted CISSS-CA ACE program improves care transitions for the elderly and by which our Wiki-suite contributes to adaptation, implementation, and scaling up of geriatric knowledge tools.

**Results:**

Data collection started in January 2019. As of January 2020, we enrolled 1635 patients and 529 caregivers from the four participating hospitals. Data collection is projected to be completed in January 2022. Data analysis has not yet begun. Results are expected to be published in 2022. Expected results will be presented to different key internal stakeholders to better support the effort and resources deployed in the transition of seniors. Through key interventions focused on seniors, we are expecting to increase patient satisfaction and quality of care and reduce readmission and ED revisit.

**Conclusions:**

This study will provide evidence on effective knowledge translation strategies to adapt best practices to the local context in the transition of care for elderly people. The knowledge generated through this project will support future scale-up of the ACE program and our wiki methodology in other settings in Canada.

**Trial Registration:**

ClinicalTrials.gov NCT04093245; https://clinicaltrials.gov/ct2/show/NCT04093245.

**International Registered Report Identifier (IRRID):**

DERR1-10.2196/17363

## Introduction

### Background

In 2019, more than one in six Canadians were aged 65 years or older. These aging Canadians will account for 20% of the population by 2024 [1]. It is a challenge for our health care system to meet the growing needs of the aging population, whose members often have chronic conditions, take multiple medications, and receive care from multiple providers. Moreover, they are typically frequent health care users, with the system spending more on them than on any other segment of the population [2]. Seniors represent a third of all patients consulting emergency departments (EDs) [3-7]. Seniors are especially vulnerable to health system failures; one-third report experiencing care coordination problems, with the most important problems according to patients being gaps in hospital discharge planning [8,9] and long waiting lists to receive home care [10,11]. Seniors and their caregivers are obliged to manage their own care through a broken care continuum [12-14]. Discharge adverse events result in unplanned readmissions [15,16], which occur after 10%-30% of medical admissions [16-28], and loss of physical, functional, and/or cognitive capacity [29-34]. Added to poor health outcomes are patient and staff distress [35,36] and increasing lawsuits concerning inadequate discharge planning [37].

### Acute Care for Elders Program: Best Practice Guidelines for Elder Care Transitions

Improving care transitions for seniors requires a multifaceted integrated approach based upon best practices [11,38], such as the Acute Care for Elders (ACE) program developed by Mount Sinai Hospital in Toronto [39-41]. Over the last decade, Mount Sinai has become Canada’s most widely recognized elder-friendly hospital, implementing evidence-informed point-of-care interventions to improve patient, provider, and system outcomes for frail older persons [2]. Supported by systematic reviews [42-48] and randomized clinical trials [49-52], the ACE care transition program is based on interprofessional interventions to enhance postdischarge care. Comparing performance in the baseline year 2009 with that in 2014, Mount Sinai reduced the total length of stay (from 12 to 8 days), reduced the alternate level of care days by 20%, reduced readmissions within 30 days (from 15% to 13%), improved the rate of patients returning home as opposed to other institutional settings (from 71% to 79%), and increased the rate of patient satisfaction (from 95% to 97%). These improvements resulted in an estimated Can $4.2 million (US $2.6 million) in savings in 2014 [53].

Unfortunately, the ACE best practice guidelines have only been implemented in a few dozen acute care organizations around the world [54]. A major barrier to their implementation is that these guidelines and tools cannot be easily transferred into different cultural, organizational, and technical contexts. Knowledge producers (researchers) and knowledge users (patients/caregivers, clinicians, and decision makers) lack effective interventions to adapt knowledge to the local context, a crucial step in the knowledge-to-action (KTA) framework [55,56]. Knowledge users lack the skills, resources, or institutional culture necessary to apply knowledge locally and support their institutions to learn new ways of operating. Researchers have been challenged to find new solutions that support the involvement of local knowledge users in adapting knowledge tools to their contexts [57-61]. Although local adaptation is a key step of the KTA framework, little is known about how to accomplish this step effectively [55,56,62,63]. New solutions are needed to support the involvement of knowledge users in adapting knowledge tools to their contexts [56-60].

### Two Novel Knowledge Translation Interventions to Adapt the ACE Program to the Local Context

In 2016, the *Centre intégré de santé et de services sociaux de Chaudière-Appalaches* (CISSS-CA) was selected by the Canadian Foundation for Healthcare Improvement (CFHI), the Canadian Frailty Network, and Mount Sinai Hospital to implement and adapt the ACE program in the local context. This adaptation also had to be performed in synergy with Quebec’s provincial elder-friendly best practices, the *Approche adaptée à la personne âgée en milieu hospitalier* (senior-friendly hospital care) [64].

A research team led by the first author (PA) and by the Chief Executive Officer (CEO) of the CISSS-CA (DP) has been using two novel knowledge translation (KT) interventions (WikiTrauma and Wiki101 [“the Wiki-suite”]) to engage knowledge users in adapting the ACE program in the local context at the Hôtel-Dieu de Lévis, one of the four acute care hospitals within the CISSS-CA. WikiTrauma [65] is a knowledge-base website on which users collaboratively modify content and structure directly from the web, which contains free web-based knowledge tools. Wiki101 [66] is a web-based training course on how to use WikiTrauma. These two interventions were initially developed for trauma care [67], and our team’s previous work has shown that these interventions are potentially effective KT interventions to support the implementation of best practices in other fields of health care [68-70].

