## Methods

### Study Design

Our study will have two main parts (Figure 1). Part 1 will involve the staggered implementation of the context-adapted CISSS-CA ACE program across four CISSS-CA sites (Hôtel-Dieu de Lévis, St-Georges, Montmagny, and Thetford Mines). We will use an interrupted time series (ITS) to measure the impact of the CISSS-CA ACE program and its context-adapted tools on all hospital-level outcomes (Table 1 and Figure 2). This design will allow us to better measure the effect of our intervention on our outcomes while controlling for secular trends in our data by comparing retrospective monthly data collected in the CISSS-CA administrative databases for 36 months before our intervention and for a maximum of 12 months after our intervention in the last targeted CISSS-CA implementation site (Hospital 4 is yet to be determined) and for up to 21 months in the first targeted CISSS-CA implementation site (Hospital 1 is the Hôtel-Dieu de Lévis). Part 2 will be a parallel mixed-methods process evaluation study to understand the underlying human, organizational, and technical factors that influence the success or failure of our intervention and, more specifically, of our Wiki-suite to facilitate it through the adaptation and uptake of geriatric knowledge tools. We will report this implementation study using the Standards for Reporting Implementation Studies (StaRI) reporting guidelines (Multimedia Appendix 1) [71]. This study has been approved by the CISSS-CA Ethics Review Committee (project #2018-462, 2018-007).

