#### Phase IB (Wiki101 and ACE Training, 3 Months)

All local team members and eligible health professionals or decision makers will complete the Wiki101 web-based training to learn how to navigate and edit knowledge tools in WikiTrauma. After completing Wiki101, our executive committee in collaboration with ACE experts will then offer tailored support to each local team and the local champions to implement the ACE program. The training and support aim to inform and empower the local teams by providing information on the various ACE program interventions to implement locally, the rationale for each program intervention, and the sharing of existing knowledge tools and expertise developed in each center.

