#### Approach

##### Phase IIA (Measurement of the Intention to Use WikiTrauma and Actual WikiTrauma Use, 9 Months)

Alongside phases IB and IC, we will conduct a theory-based process evaluation. All Wiki101 participants will be invited to answer a validated Theory of Planned Behavior questionnaire [95] at baseline before Wiki101, immediately after Wiki101, and at the end of Phase ID to measure the change in intention and the impact of Wiki101 on Theory of Planned Behavior determinants. We will also use Google Analytics to track the use of WikiTrauma tools by the participants over time. Segmented regression statistics will be used to measure the changes in the level and slope for postintervention Wiki use compared with preintervention Wiki use [92].

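### Some Hôtel-Dieu de Lévis respondents may have met WikiTrauma or Wiki101 before the study, so their questionnaire before Wiki101 may not be a first-exposure baseline

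*Protocol article*

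**What the plan says.** **Earlier use.** The abstract's Background states: "In 2016, a context-adapted ACE program was implemented at one hospital". It adds that this quality improvement project relied on the Wiki-suite to involve stakeholders. The Introduction section on the two knowledge translation interventions names both parts of the suite, the WikiTrauma site and the Wiki101 course. It says they were being used "to engage knowledge users in adapting the ACE program in the local context at the Hôtel-Dieu de Lévis". The preceding Introduction section, on the ACE guidelines, counts patients and caregivers, clinicians, and decision makers as knowledge users.

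**Same hospital in the study.** Study Design states: "Hospital 1 is the Hôtel-Dieu de Lévis".

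**Who is trained.** Phase IB states: "All local team members and eligible health professionals or decision makers will complete the Wiki101 web-based training". No exception is given for people trained earlier.

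**Who is surveyed, and why.** Phase IIA states: "All Wiki101 participants will be invited to answer a validated Theory of Planned Behavior questionnaire". The questionnaire is given before the course, directly after it, and at the end of Phase ID. Its purpose is "to measure the change in intention and the impact of Wiki101 on Theory of Planned Behavior determinants". No control group is stated for this comparison. The article does not say whether scores are analysed together, by site, or by earlier exposure.

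**The concern.** An uncontrolled before-after contrast measures the effect of a course only if the first measurement precedes exposure to it. At one of the four hospitals, both the tool and the course were in use before the study phases. A Lévis respondent who had already edited WikiTrauma or completed Wiki101 may start with intention scores already shifted by that contact. The change recorded for that person is then the effect of a second exposure, not the first.

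If such people have less room to change, counting them alongside newcomers pulls the average change toward zero. A small change could then be read as weak training when it partly reflects earlier training. What is at stake is the interpretation of one quantitative process measure for Objective 3, the objective on how the Wiki-suite supports adaptation and local uptake of tools.

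**Working it through.** The article gives no sample size, effect size or error rate for this questionnaire, so there is no stated figure to reproduce. The check has two parts.

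**1. Do the exposed group and the surveyed group overlap?**

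- Exposed before the study: knowledge users at Hôtel-Dieu de Lévis, a term that includes clinicians and decision makers (Introduction).
- Trained in the study: local team members and eligible professionals or decision makers at each site (Phase IB), with Lévis as the first site (Study Design).
- Surveyed: all Wiki101 participants (Phase IIA).

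The groups overlap by role and by hospital. How many individuals belong to both is not stated. People involved in the earlier adaptation would be natural candidates for the local team or as champions, but that is inference.

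**2. How large could the effect be?**

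Take a simple mixture with three assumed inputs, none of them in the article:

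- s = Lévis share of all respondents
- e = fraction of Lévis respondents with earlier exposure
- r = their change relative to that of first-exposure respondents (0 = no further change, 1 = the same change)

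If all respondents are averaged together:

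observed change ÷ first-exposure change = 1 − s × e × (1 − r)

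| s | e | r | Calculation | Ratio | Dilution |
|---|---|---|---|---|---|
| 0.25 | 0 | any | 1 − 0 | 1.00 | 0% |
| 0.25 | any | 1 | 1 − 0 | 1.00 | 0% |
| 0.25 | 0.25 | 0 | 1 − 0.0625 | 0.94 | 6% |
| 0.25 | 0.5 | 0 | 1 − 0.125 | 0.875 | 12.5% |
| 0.25 | 1 | 0.5 | 1 − 0.125 | 0.875 | 12.5% |
| 0.25 | 1 | 0 | 1 − 0.25 | 0.75 | 25% |
| 0.5 | 0.5 | 0 | 1 − 0.25 | 0.75 | 25% |
| 0.5 | 1 | 0 | 1 − 0.5 | 0.50 | 50% |

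The value s = 0.25 stands for four equal sites, and s = 0.5 for Lévis supplying half the respondents. The dilution is zero if nobody was exposed earlier, or if exposed respondents change as much as newcomers. Limiting r to the range 0 to 1 is itself an assumption.

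**The case against.** The strongest reply is that the article leaves too much open for an error to be shown, and much of it stands.

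- **Extent of exposure.** A reader might infer that Lévis staff in general had already worked with both tools. The text says only that the tools were used to engage knowledge users, a group that also includes patients and caregivers. It does not say how many staff were reached or whether anyone had completed Wiki101. Nor does it say whether people who took the course earlier would repeat it and be surveyed again.
- **Pooling.** A reader might infer that the four hospitals will be averaged together. The article does not say so, and a fuller plan may analyse by site or by earlier exposure.
- **Between-hospital comparison.** A reader might expect Lévis to be ranked as the site where training worked least. No comparison of intention scores between hospitals is planned. Phase IIC compares barriers, facilitators and local solutions.
- **Weight.** The questionnaire sits beside tracked WikiTrauma use, at least 32 interviews, document analysis and the case-study comparison. It is not the main test of Objective 3.
- **Condensed format.** The questionnaire is not reproduced, so it may already ask about earlier use.

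What the reply does not remove is the definition that the article itself gives. The baseline is fixed only by its place before the study course, its population is all participants, and its target is the impact of that course. One of the four sites began with the same course and tool already in use. A site-specific analysis alone would not resolve this, because exposed and unexposed people may be mixed within Lévis. Separating them requires information on each person's earlier exposure.

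**Conclusion.** The point holds in a limited form. Some Lévis clinicians and decision makers may have used WikiTrauma or completed Wiki101 in the adaptation project begun in 2016. For any such respondent, the first questionnaire is not a naive baseline. Followed as written, the all-participant contrast could count the effect of re-exposure as the impact of the training, and may understate the first-exposure effect on intention.

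The 25% and 50% upper figures require that every Lévis respondent was exposed earlier and shows no further change. A reader might conclude that the estimate is biased toward no effect. The documents support only the possibility, with a plausible direction.

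This is a cheap improvement to a process-evaluation measure. The primary outcome, the composite of 30-day readmission and ED visits, is unaffected.

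**What to change.** 1. Record earlier Wiki101 completion and earlier WikiTrauma use for each participant, by one item in the baseline questionnaire unless it already asks this. If the Lévis baseline has been collected, use one retrospective question, supported by the wiki's tracked history. That history records changes to content, so on its own it may miss people who only read the wiki or took the course.
2. Estimate the effect of Wiki101 on intention mainly in first-exposure participants: those at the other three hospitals plus Lévis participants without earlier exposure, with exposure status taken from the recorded item.
3. Report previously exposed participants separately, as a description of repeat exposure.

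The cost is one question and one stratified analysis. The downside is a somewhat smaller main analysis set, by a number the article does not allow one to estimate. A retrospective question also carries some recall error.

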### Objectives

The goal of this study is to improve transition care for seniors within the CISSS-CA. Specifically, it aims to (1) implement a context-adapted CISSS-CA ACE program in its four EDs and measure the impact on patient-, caregiver-, clinical-, and hospital-level outcomes; (2) identify underlying mechanisms by which our context-adapted CISSS-CA ACE program improves care transitions for elderly people; and (3) identify underlying mechanisms by which the Wiki-suite contributes to context adaptation and local uptake of knowledge tools.

## Methods

### Study Design

Our study will have two main parts (Figure 1). Part 1 will involve the staggered implementation of the context-adapted CISSS-CA ACE program across four CISSS-CA sites (Hôtel-Dieu de Lévis, St-Georges, Montmagny, and Thetford Mines). We will use an interrupted time series (ITS) to measure the impact of the CISSS-CA ACE program and its context-adapted tools on all hospital-level outcomes (Table 1 and Figure 2). This design will allow us to better measure the effect of our intervention on our outcomes while controlling for secular trends in our data by comparing retrospective monthly data collected in the CISSS-CA administrative databases for 36 months before our intervention and for a maximum of 12 months after our intervention in the last targeted CISSS-CA implementation site (Hospital 4 is yet to be determined) and for up to 21 months in the first targeted CISSS-CA implementation site (Hospital 1 is the Hôtel-Dieu de Lévis). Part 2 will be a parallel mixed-methods process evaluation study to understand the underlying human, organizational, and technical factors that influence the success or failure of our intervention and, more specifically, of our Wiki-suite to facilitate it through the adaptation and uptake of geriatric knowledge tools. We will report this implementation study using the Standards for Reporting Implementation Studies (StaRI) reporting guidelines (Multimedia Appendix 1) [71]. This study has been approved by the CISSS-CA Ethics Review Committee (project #2018-462, 2018-007).

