## Discussion

### Principal Findings

Our study will produce a new partnership among patients, clinicians, and decision makers, engaging and empowering them to improve care for elderly people by implementing the CISSS-CA ACE program in four hospitals within the CISSS-CA. This study will also provide qualitative and quantitative evidence on effective strategies for improved transition care for elderly people. This study specifically aims at decreasing CISSS-CA’s 30-day rate of readmission for elderly patients, which has been increasing since 2014 (13% in 2014 and 16% in 2016), and its high 30-day ED visit rate (21% in 2014 and 22% in 2016). Our team will generate real-time quality improvement data that will guide decision-making by the CISSS-CA and help adjust resource allocation and policy-making that will positively influence future care transitions for elderly people.

Our study will also identify the human, organizational, and technical factors that support the local adaptation of knowledge and the scale-up of our intervention in other care settings within the CISSS-CA and elsewhere in Canada [101,102]. This will contribute to making the CISSS-CA a learning organization and to training a new cadre of clinicians, administrators, policy-makers, and scientists who will transform our health system [103]. This is also highly relevant to INESSS and CFHI, who aim to scale up innovations and best practices in the care of seniors in Quebec and Canada, respectively.

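### Hospital 1 (Hôtel-Dieu de Lévis) very probably had an ACE program from 2016, so none of its 36 baseline months is clearly unexposed and its contrast is at best incremental

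*Protocol article*

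**What the plan says.** The Abstract (Background) states: "In 2016, a context-adapted ACE program was implemented at one hospital", "with a focus on improving transitions between hospitals and the community". The hospital is not named there. The Introduction, in the section on the two knowledge translation interventions, places the organization's selection for the ACE work in 2016. It says the team has been using the Wiki-suite "to engage knowledge users in adapting the ACE program in the local context at the Hôtel-Dieu de Lévis". No other hospital is mentioned in that connection.

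Methods, Study Design, makes the same hospital the first site of the interrupted time series, followed "for up to 21 months in the first targeted CISSS-CA implementation site (Hospital 1 is the Hôtel-Dieu de Lévis"). The baseline is "retrospective monthly data collected in the CISSS-CA administrative databases for 36 months before our intervention". The last site is followed "for a maximum of 12 months after our intervention in the last targeted CISSS-CA implementation site".

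Study Comparison makes each centre's own preintervention results the comparator. Sample Size and Statistical Analysis specifies segmented regression with a change in level and slope for each centre. The Limitations section does not mention earlier ACE exposure at any site.

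**The concern.** An interrupted time series projects the baseline forward as the course expected without the intervention. That works only if the baseline months were free of it. The study intervention is a context-adapted ACE program delivered through the Wiki-suite, and the 2016 project is described in the same terms with the same aim of better transitions. If that project ran at Hospital 1, the months labelled preintervention there are months with some version of the program in place.

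Two things are at stake for the primary outcome at the site with the longest follow-up. The first is the estimand: the contrast would show what the new roll-out adds to the 2016 program, not what the program does. The second is the baseline trend: if the 2016 change falls inside the 36 months, a single straight baseline line absorbs it as slope, and the projection is wrong even for the increment.

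**Working it through.** **Inputs from the article**
- Earlier program: 2016, month not given (Abstract).
- Data collection from January 2019, projected to end in January 2022 (Results).
- Recruitment starts at least 3 months before phase IA at each site (Patient and Caregiver Recruitment).
- Phases IA, IB and IC take 3 months each, so active implementation (phase ID) follows phase IA by 9 months.
- Hospital 1: 36 months before, up to 21 after.

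**Are the stated windows consistent with the dates?** The first and last sites differ by 21 − 12 = 9 months, which fits three 3-month steps over four sites. A 21-month follow-up ending by January 2022 needs a start by April 2020. The earliest phase IA is January 2019 + 3 = April 2019, and the earliest phase ID is April 2019 + 9 = January 2020. The windows therefore fit.

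**Where does the baseline fall?** It runs from 36 months before the start to the month before it.

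| Assumed start at Hospital 1 | Baseline | Before 2016 | In 2016 | After 2016 |
|---|---|---|---|---|
| April 2019 (earliest phase IA) | Apr 2016 – Mar 2019 | 0 | 9 | 27 |
| January 2020 (earliest phase ID) | Jan 2017 – Dec 2019 | 0 | 0 | 36 |
| April 2020 (latest start leaving 21 months) | Apr 2017 – Mar 2020 | 0 | 0 | 36 |

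Even a start in January 2019, which ignores the 3-month lead-in, gives January 2016 to December 2018. A month before 2016 would need a start before January 2019, which conflicts with the stated dates.

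**Case A: the 2016 start precedes the window.** Let the full effect against no ACE be −1, with a share f already present throughout the baseline. The estimated level change is −(1 − f): −0.75, −0.50, −0.25 and 0 for f = 0.25, 0.50, 0.75 and 1. Bias for the increment is zero.

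**Case B: a lasting drop of δ after k complete baseline months.** This is noise-free least squares with 36 points before and 21 after, and no further change at the new start.
- Baseline slope = −6k(36 − k)δ / [36(36² − 1)]
- Baseline mean = −(36 − k)δ/36, centred at month index 17.5
- Projection to the first post month (index 36) = mean + 18.5 × slope
- Spurious level change = −δ − projection
- At the 12th post month, subtract a further 11 × slope

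In a window opening in April 2016, the latest step still in 2016 is December, so k = 8:
- slope = −6·8·28/(36·1295) δ = −0.0288δ
- mean = −28/36 δ = −0.778δ
- projection = −0.778δ − 18.5·0.0288δ = −1.311δ
- level bias = **+0.31δ**
- 12-month bias = 0.311δ + 11·0.0288δ = **+0.63δ**

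Earlier steps give less: k = 3 gives +0.15δ and +0.29δ, and k = 6 gives +0.26δ and +0.52δ. These are biases in the increment, towards apparent harm when δ is a benefit.

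**Case C: the earlier effect fades.** With a full effect of −1, and half of it present at the start of the window but fading linearly to nothing, the level change stays at −1.0. The mean post effect is −1.14, so the program's effect is overstated.

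**The case against.** Several counter-arguments have force.

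- **Identity and extent.** The Abstract does not name the 2016 hospital. The earlier work is called a quality improvement project based on iterative prototyping, and the Introduction describes adaptation as continuing. Nothing says which of the nine components listed under phase ID ran at Lévis, or from what month. A reader might infer that the whole baseline was fully exposed. The text supports only exposure of unknown extent.
- **Direction.** A reader might infer that Hospital 1's result must be biased against the program. It need not be. Counted from phase ID, the window opens in January 2017 at the earliest. A lasting 2016 step then precedes it, and the increment is estimated without this bias.
- **Spread to the overall result.** A reader might also infer that Hospital 1 dilutes a pooled estimate. The article states models for each centre and a comparison across the four centres. It states no pooled effect, so the other three series are not contaminated.
- **What belongs in an analysis plan.** Extra breakpoints and leave-one-site-out analyses are commonly specified there. But the article itself fixes the 36-month window and the own-baseline comparator and calls that baseline preintervention, and that label is what fails at Hospital 1.
- **A longer baseline is no simple cure.** Going 36 months behind a 2016 start reaches 2013 and crosses the 2015 reform that created the organization (Study Context). The readmission figures in Principal Findings, "13% in 2014 and 16% in 2016", are rates for the whole organization. They do not show that monthly data for Lévis exist that far back.

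These points limit the size, direction and reach of the problem. They do not supply an unexposed baseline for Hospital 1.

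**Conclusion.** The point stands for one of the four site series. On every start date the text allows, 36 of 36 Hospital 1 baseline months lie in or after 2016, so the planned comparison there cannot be read as the effect of the program against no program.

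The consequence depends on the unstated start month. If the 2016 start precedes the window, the result is an incremental effect. If a lasting beneficial step lies inside a window opening in April 2016, the bias against the program reaches about 0.31δ in level and 0.63δ at 12 months. δ is unknown, so no absolute bias can be given, and a fading earlier effect could reverse the sign.

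This rests on three assumptions: that the 2016 hospital was Hôtel-Dieu de Lévis (a strong inference), that the written dates govern (the calendar in Figure 1 could not be read for this check), and, for the bias figures, that the 2016 change was a single step.

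**What to change.** In Study Design, Study Comparison and Sample Size and Statistical Analysis:

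1. Give the month in which the 2016 program started at Hôtel-Dieu de Lévis and the components then in place, and declare Hospital 1 previously exposed.
2. If the 2016 start lies in the 36-month window, model it as an additional breakpoint or interruption period.
3. Interpret the Hospital 1 result as an incremental effect over the 2016 program.
4. Base the conclusion about the program's effect on the three hospitals without earlier exposure. Report Hospital 1 separately and add it in a sensitivity analysis.
5. Where monthly Hospital 1 data from before 2016 exist, use a longer baseline as a supporting analysis that allows for the 2015 reorganization.

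The cost is some loss of precision in any cross-site summary and a little more analysis. The article reports that data analysis had not begun, so the change could still be prespecified at that point.
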